### Intervention

The intervention, primarily based on the pilot intervention was co-developed by a multidisciplinary team comprised of academic and end-user stakeholders from government health agencies, educational systems employees, universities and technology partners and parent representatives with expertise in nutrition, school based health intervention, behaviour change, implementation science and technology based interventions.

The intervention was developed using the Behaviour Change Wheel (BCW) [32]. The BCW consolidates 19 frameworks of behaviour change and provides a process to move from behavioural diagnosis to intervention design. The BCW recommends thorough formative evaluation to identify impediments to behaviour change and to select appropriate behaviour change techniques to address these. Accordingly, extensive formative research was conducted to identify barriers and potential behaviour change techniques that may support parents to pack healthy school lunchboxes. Specifically, the team undertook a review of published literature of existing lunchbox interventions [20], conducted focus groups with parents to identify local contextual barriers, and undertook telephone interviews with parents (*n* = 228) ([name], [name], [name], [name], [name], [name], [name]: Parent acceptability of using a mobile phone application to promote healthy lunchboxes for childcare- and school-aged children, unpublished) and principals (*n* = 196) [33] to assess barriers, and the acceptability of potential intervention strategies, content and delivery modalities. Based on such evidence, the BCW was used to select the most promising intervention strategies (behaviour change techniques) to address the most pertinent barriers to packing healthy lunchboxes.

Table 1 outlines the barriers identified via the formative research phase.

**Table 1 Tab1:** Identified barriers to packing a healthy lunchbox

	Setting (school)	Family (parental)	Individual (child)
Barriers	• Food safety regarding lack of refrigeration and reheating facilities at school [34, 35] • School allergy policy [35] • Accessibility of fresh produce [35] • Availability of discretionary food and drink products [36] • Advertising and packaging [34, 36]	• Time to prepare lunchbox [34] • Cost and affordability and perception that healthy food is more expensive [34] • Poor nutritional knowledge on healthy food products [34] • Negative parental modelling [37] • Conflicting food purchases [37] • Parental food preferences [37] • Lack of skills in cooking and preparing food [37] • Convenience [34, 37] • Discretionary food provision as a reward for good behaviour [37] • Lack of social support [36] • Social norms and cultural challenges [36]	• Child preference and fussy eating [34] • Attitude [36] • Food and beverage likes and dislikes [36] • Parental pressure to offer what the child prefers [36]

Minor modifications to the SWAP IT intervention were made following the pilot RCT which established potential efficacy, feasibility and acceptability in 12 Catholic primary schools, including minor wording and formatting changes to the push notifications, updates to the associated webpage, parent resource and flipcharts to include Aboriginal artwork and updated graphics and short professional learning module for school staff. A description of the intervention logic model is provided in Fig. 2.

**Fig. 2 Fig2:**
[figure not shown]
SWAP IT logic model

The SWAP IT intervention encourages ‘swaps’ from discretionary food items to guideline-based healthier alternatives known as ‘everyday’ foods, with the m-health component (weekly pushed messages to parents) delivered via an existing school mobile communication app, Skoolbag. Schools purchase the SkoolBag app for a nominal fee annually and require parents to download an android or IOS version (free for parents) to receive direct school communication such as school reminders and notes regarding school events and student progress.

The intervention involves:
*Lunchbox nutrition guidelines*: Participating schools will be asked to adopt and endorse lunchbox nutrition guidelines, consistent with the WHO and the NSW Department of Education Nutrition in Schools policy [38]. A guideline template will be provided to support schools to communicate to the school community. Principal endorsement of guidelines will be promoted to the school community via the SkoolBag app and school newsletters, utilising the authority of the school Principal, to communicate school expectations and normalise healthy lunchboxes. In the pilot, 85% of schools adopted and endorsed such guidelines. With support from a trained dietitian, the development of lunchbox nutrition guidelines will occur in the first term (5 school weeks) of the intervention.*Weekly support messages*: An existing school mobile communication app (SkoolBag) will be used to communicate healthy lunchbox messages to parents/carers. Through the SkoolBag app, content to support the packing of healthy lunchboxes will be sent to parents/carers at weekly intervals over the second school term (10 weeks) via push notifications (electronic messages). The messages are designed to act as prompts and cues to reinforce packing of ‘everyday’ foods children enjoy, provide tips and suggestions to assist parents to pack ‘everyday’ foods that are quick, convenient and low cost, and connect parents with tools and resources to improve their knowledge and skills to swap out discretionary foods and pack ‘everyday’ foods. The messages and embedded videos provide simple instructions on swapping, demonstrate the time needed to pack healthy lunchboxes and assist parents to plan healthy lunchbox swaps. Distribution of the messages via SkoolBag will be managed by the project team, not requiring school time or resources. In the pilot intervention, all ten messages were delivered to all parent users of the SkoolBag app in all schools resulting in the delivery of 11,500 messages to parents [23].*Resources for parents*: Links embedded in the app messages will connect parents to additional resources housed on the program website. These resources provide parents with information regarding health consequences, simple instructions on making healthy lunchbox swaps, and assist in lunchbox planning to address child preference, cost, convenience and food safety. Additional physical resources including a SWAP IT ideas booklet (lunchbox ideas), clear drink bottle for water and an ice-brick to support food safety concerns will also be provided to parents.*Curriculum resources for schools*: Schools will be provided with a short teacher professional learning session outlining the rationale for the study and providing the skills and resources required to deliver the classroom curriculum lessons. Teachers will be provided complimentary stage appropriate curriculum resources and classroom flipcharts, developed by dietitians in consultation with teachers to align with syllabus outcomes to reinforce program messages. The resources are designed to reinforce healthy food preferences and improve students’ nutrition knowledge.

### Control

Schools allocated to the control group will participate in data collection only. They will have access to the app but none of the lunchbox intervention content.

### Data collection procedures and measures

All schools will be offered 1 day of teacher relief funding (AUD$400) to reimburse the school for their time in assisting with data collection over the intervention period.

### Primary outcome

Mean energy (kJ) content of discretionary foods packed from the school lunchboxes will be assessed using a valid and reliable lunchbox observational audit, known as the School Food Checklist (SFC), [39, 40] an approach successfully applied in the pilot and deemed highly feasible in assessing foods packed in the lunchbox resulting in 98% of lunchbox photographs being included in the analysis and will be extended to also assess consumption by taking a second photo at the end of the final school break period. On a randomly selected school day, prior to recess, lunch and in-class vegetable and fruit breaks (pre meal assessment) [41, 42], students will be asked to display their lunchbox on their desk and remove all lids from storage containers. To prevent response bias, parents or students will not be aware of the day of data collection. Trained research assistants will take a photograph of each student’s lunchbox at the beginning of the school day prior to any contents being consumed (“foods packed”) and will also write down any ambiguous items to aid analysis. Students will also be asked if they intend to purchase from the canteen that day.

Students will be asked to place unconsumed or partially consumed items back into their lunchbox, after each meal break (in-class vegetable and fruit breaks, recess and lunch). A second photograph will be taken following the final meal break (post meal assessment). Measures of energy consumption will be calculated by subtracting the energy content of foods and drinks remaining in student’s lunchbox at the post-meal assessment from the energy content of foods and drinks in the lunchbox during pre-meal assessment (“foods consumed”).

The SFC is a previously validated tool shown to be accurate and reliable in measuring energy from food and drinks for the Australian context. The SFC [39, 40] enables assessment of the kJ content and serving size for each lunchbox item. The checklist includes 20 food and drinks categories including main food items such as bread, fast food and leftovers/mixed dishes and snack items such as noodles, packaged snacks, biscuits and crackers, chocolate and lollies, cheese, eggs, dried fruit and nuts, muesli and fruit bars, cakes and buns, muffins and scones, pastries, desserts, yoghurt, fruit, vegetables, milk, soft drink, water and fruit juice. Foods in each category were included based on the frequency of consumption at school for children aged five to 15 years, according to the National Nutrition Survey 1995 [39] and the average kJ per category identified. The SFC will be used to identify the total lunchbox contents and food items in the lunchbox including the kJ content, number of ‘everyday’ or discretionary lunchbox items and the mean cost of lunchbox items. Everyday items refer to food and drink items that are part of the core food groups as determined by the Australian Dietary Guidelines and Australian Guide to Healthy Eating [4]. Food items classified as discretionary choices are items considered to be energy dense with minimal nutritional value such as cakes, chocolate, lollies, crisps, muesli bars and fast food.

Minor modifications were made to the SFC to separately categorise ‘everyday’ and discretionary food choices and updated to reflect the mean cost of lunchbox items at the time the pilot study was conducted (2017). Categories that required adjustment included: biscuit and crackers, cakes and buns, muffins and scones, desserts and packaged snacks. All foods in these categories were individually divided and categorised as an ‘everyday’ or discretionary food by consensus among dietitians. The serve size and kJ per serve information was obtained from FoodWorks Professional Edition V7 (version 7; Xyris Software, Highgate Hill, QLD, Australia), or if unavailable from FoodWorks, via a snack food database created for pre-packaged items. The snack food database was created by dietitians based on a significant array of pre-packaged snacks available in Australian supermarkets and included detailed nutrition information for each food item.

Trained dietitians will observe each school lunchbox photo and classify each food and drink item according to its SFC category and the serving size. To further aid this process, decision rules developed will be used to ensure standardisation of assessments. Following the analysis of the pre-meal lunchbox photo, dietitians will analyse the post meal photo.

Students who make canteen purchases on the day of data collection will be excluded from analysis. Primary outcome data will be collected at baseline and immediately post intervention (5 months).

### Secondary outcomes

a) mean total energy (kJ) packed within the lunchbox; b) mean total energy (kJ) consumed from the lunchbox; c) mean energy (kJ) from discretionary foods and drinks consumed within the lunchbox; d) mean energy (kJ) from healthy foods packed and consumed from the lunchbox and e) percentage of lunchbox energy from discretionary and healthy foods and drinks, both packed and consumed, will be assessed using the above mentioned measures and procedures. Measures relating to the food packed will be based on the first photograph taken at the beginning of the school day, prior to the consumption of any food items. Measures relating to consumption will be based on the second photograph of the day being taken, after all meal breaks have occurred and all uneaten food is placed back into the lunchbox container.

#### Student school engagement

As school engagement including behavioural, emotional and cognitive engagement is considered crucial for achieving positive academic outcomes [43], at baseline and follow-up, students in years 5 and 6, as part of their student survey, will be asked to complete selected items from the validated School Engagement Measure (SEM) – MacArthur [43]. The SEM is a 19 item survey which will provide a measure of students’ behavioural (5 items), emotional (6 items) and cognitive engagement (8 items) at school.

#### Student consumption of discretionary foods outside of school hours

Whilst the purpose of the SWAP IT intervention is to decrease the mean energy content of discretionary foods packed within a school lunchbox, to identify any compensatory nutrition behaviour occurring out of school hours, parents will be asked to report via a short telephone survey, at baseline and follow-up, on their child’s nutritional intake outside of school hours and on weekends. Measures will be taken from the NSW Schools Physical Activity and Nutrition Survey (SPANS 2015) [6]. Additionally, an exploratory sub study will be conducted to assess mean daily nutrient consumption in consenting students from Years 5 and 6, who reliably self-report [26] at baseline and immediately post intervention at 5 months using the Australian Child and Adolescent Eating Survey (ACAES) [26] completed in class time via a pen and paper survey and facilitated by a trained research assistant. Pen and paper surveys will be provided for students to complete taking approximately 40 min. This food frequency questionnaire is a valid and reliable tool to identify usual dietary consumption, mean energy and nutrient intake over the past 3 months, and percentage energy from food groups including discretionary foods to aid in characterising any intervention effects [26]. The ACAES has been validated in students aged between nine and 16 years from the Hunter region in NSW and recommended for use in intervention trials [26]. The measurement of student consumption is for exploratory purposes, not powered to detect effects and intended for descriptive purposes, to describe any changes in the dietary behaviour of children outside of school hours.

#### Implementation outcomes

Consistent with the hybrid design, to identify if the intervention was implemented as intended and to inform future scale-up efforts the following implementation outcomes will be measured, based on the Proctor et al. [44] taxonomy of implementation outcomes. This includes:
▪ *Acceptability*: At follow-up, school principals will be requested to participate in a short interview where they will be asked the acceptability of the SWAP IT intervention in their school. Via a telephone interview, parents will also be asked about the acceptability of SWAP IT, based on Acceptability of Intervention Measure (AIM) [45], developed by Weiner et al., a four-item valid and reliable scale. The research team have achieved high school (77.8–96.4%) [23] and parent (74%) consent rates for telephone surveys.▪ *Adoption*: Via the Principal interview, principals will be asked if the school adopted the lunchbox nutrition guidelines and asked for evidence of promotion to the school community. Parents will be asked if they had made any healthy swaps in the lunchbox based on the information received via the SWAP IT intervention via the parent telephone interview.▪ *Appropriateness*: At follow-up, intervention principals (interview) and parents (telephone survey) will be asked questions related to intervention appropriateness via the Intervention Appropriateness Measure (IAM), a four-item valid and reliable scale [45].▪ *Feasibility*: At follow-up, intervention principals (via interview) and parents (via telephone survey) will be asked to complete the Feasibility of Intervention Measure (FIM), a four-item valid and reliable scale [45].▪ *Fidelity:* Project records, app analytics, as well as post-intervention measures completed by intervention principals (interview) and parents (telephone survey) will be used to determine the proportion of schools and parents that received and attended to each of the implementation strategies.▪ *Implementation cost:* see cost and cost-effectiveness measure below.▪ *Penetration:* Penetration will also be measured via reviewing app analytics, via the number of teachers who use the curriculum lessons within class and via the percentage of student consenting to participate in the evaluation component of the program.▪ *Identification, measurement and valuation of resource use*: Resource use data pertaining to the development and implementation of the intervention will be collected prospectively using a bespoke cost capture tool developed in MS Excel (2013). Costs will be denominated in 2019/20 Australian dollars ($). Labour time and materials will be valued using market rates. Additionally, the cost of food and drink items packed within lunchboxes will be included in the SFC.▪ *Cost-Effectiveness and budget impact analysis*: Subject to assessment of efficacy, a cost-effectiveness analysis will be conducted from multiple stakeholder perspectives comparing the intervention to a usual practice counterfactual. The primary cost-effectiveness outcome will be incremental cost per unit change in mean energy content of foods. In addition, the public finance budget impact to scale-up the SWAP IT intervention across NSW will be modelled.

### Sample size and power calculations

Based on our pilot results, a standard lunchbox contains 1089 kJ (SD = 900 kJ) from discretionary foods. With an ICC of 0.05, 36 schools with 140 students per school will enable detection of a 200 kJ difference between groups at follow-up on the primary trial outcome, with 80% power at the 0.05 significance level. As approximately 420 kJ across a whole day has potential to reduce the prevalence of childhood obesity [18, 19], and a child consumes a third of their daily energy requirements whilst at school [11], this magnitude of effect is considered meaningful at a population level.

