**Methods:**

A Type I hybrid effectiveness-implementation cluster randomised controlled trial will be conducted in up to 36 primary schools in the Hunter New England, Central Coast and Mid North Coast regions of New South Wales, Australia. Designed using the Behaviour Change Wheel, schools will be randomly allocated to receive either a 5-month (1.5 school terms) multi-component intervention that includes: 1) school lunchbox nutrition guidelines; 2) curriculum lessons; 3) information pushed to parents via an existing school-based communication application and 4) additional parent resources to address common barriers to packing healthy lunchboxes or a control arm (standard school practices). The study will assess both child level dietary outcomes and school-level implementation outcomes. The primary trial outcome, mean energy (kJ) content of discretionary lunchbox foods *packed in children’s lunchboxes*, will be assessed at baseline and immediately post intervention (5 months or 1.5 school terms). Analyses will be performed using intention to treat principles, assessing differences between groups via hierarchical linear regression models.

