### Recruitment

#### Schools

Primary schools catering for students from Kindergarten to Year 6 will be eligible for inclusion if they meet the following criteria: Government schools; located in one of the participating LHD; greater than 120 student enrolments; current users of the preferred school mobile communication app (SkoolBag); and not participating in other nutrition based research studies. Central and secondary schools catering for students aged 13–18 years and schools primarily catering for children with special needs (such as intellectual disabilities) will be excluded. Eligible schools will be randomly ordered using a random number generator in Excel to randomise the order of schools approached and sent a letter of invitation. One week following the invitation, a member of the research team will contact the principal via telephone and seek consent. A face-to-face meeting will also be offered to all schools to outline the requirements of the study. Recruitment will continue until 36 schools consent to participate (see Fig. 1).

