#### Parents and children

The child/parent recruitment strategy was developed based on our pilot study and reviews of evidence for facilitating participation in school-based research [23, 28]. Following recruitment of schools, all parents with a child enrolled in Kindergarten to Year 6 in consenting schools will be invited to participate in the study evaluation measures. Students will be provided with an information package containing an outline of the study and a consent form. Active parental consent will be required for child participation and parents will be asked, via the consent form, if they are an active user (i.e. downloaded the app) of the school communication app. One week following distribution of the information package, parents who have not returned a consent form will be telephoned by school-employed staff and asked if their child can participate in evaluation measures. A replacement consent form will be sent to parents who provide verbal consent. The research team have experience in recruiting schools and parents using such methods, obtaining response rates of 70–80% in previous trials [29].

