### Analysis

All statistical analyses will be performed using SAS (version 9.3) statistical software. Using intention to treat principles, differences between groups in both costs and outcomes will be assessed using hierarchical linear (or logistic for binary outcomes) regression models, adjusting for pre-specified prognostic variables and random effects for repeated measures on students. Missing data will be imputed using multiple imputation methods. All statistical tests will be two tailed with an alpha of 0.05. Students intending to purchase their lunch from the canteen will be removed from the primary analysis to focus on students whose lunchbox is their sole source of energy for the day [23].

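### The stated 80% power for 200 kJ holds only under a normal approximation with 36 equal schools of 140 analysed pupils; a calculation that respects 36 randomised schools gives about 75–78% unadjusted

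*Protocol article*

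**What the plan says.** The section Sample size and power calculations takes its variability from the pilot: "a standard lunchbox contains 1089 kJ (SD = 900 kJ) from discretionary foods". With an ICC of 0.05 it concludes that "36 schools with 140 students per school will enable detection of a 200 kJ difference between groups at follow-up", "with 80% power at the 0.05 significance level". The Analysis section adds: "All statistical tests will be two tailed with an alpha of 0.05". Sample and participants gives 18 schools per arm, and Randomisation and blinding makes the school the unit of allocation.

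Other sections bear on whether 36 schools of 140 is what will be analysed:

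- Recruitment, Schools: the size criterion is "greater than 120 student enrolments". No upper limit or expected mean is given. Recruitment continues until 36 schools consent.
- Recruitment, Parents and children: active parental consent is required, and the team reports "obtaining response rates of 70–80% in previous trials".
- Primary outcome and Analysis: pupils who buy, or intend to buy, from the canteen are removed. In the pilot 98% of photographs were usable.
- Abstract, Methods: the trial "will be conducted in up to 36 primary schools", which makes 36 a maximum. Design, Sample and participants, Recruitment and the sample size section all treat 36 as the number.

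The abstract's Discussion describes the trial as fully powered.

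**The concern.** With only 36 randomised schools, a normal-theory formula overstates power, because the treatment contrast is judged against variation between schools. The formula also assumes equal clusters, whereas the eligibility rule admits any school above 120 enrolments and so guarantees unequal ones. A school at the floor cannot supply 140 consenting pupils at the quoted consent rates. If the stated figure already uses every school and all 140 pupils, each departure takes power below 80%.

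At stake is how a null or borderline result is read. A reader told that the trial was fully powered for 200 kJ would take a non-significant result as stronger evidence against that effect than the design provides.

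**Working it through.** **Inputs from the protocol article.** Difference 200 kJ, SD 900 kJ, ICC 0.05, 18 schools per arm, 140 pupils per school, two-sided alpha 0.05.

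**1. Reproduce the stated figure.**
- Design effect = 1 + (140 − 1) × 0.05 = 7.95.
- Effective number per arm = 18 × 140 / 7.95 = 2520 / 7.95 = 317.0.
- SE of the difference = 900 × √(2 / 317.0) = 71.5 kJ.
- Normal power: 200 / 71.5 = 2.80; 2.80 − 1.96 = 0.84; power 79.9%.
- In reverse: 318 per arm are needed under individual randomisation, and 318 × 7.95 / 140 = 18.06 schools per arm against 18 planned.

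So 80% reproduces, with no slack.

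**2. Same inputs, t reference.** Degrees of freedom = 36 − 2 = 34. Noncentral t with noncentrality 2.80 gives power 77.6%. The detectable difference at 80% power is about (2.032 + 0.852) × 71.5 = 206 kJ. This step needs no assumption from outside the document.

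**3. What the recruitment rules yield.**
- A school of 121 pupils gives 121 × 0.70 = 85 to 121 × 0.80 = 97 consenting pupils.
- To have 140 consenting pupils, a school needs 140 / 0.80 = 175 to 140 / 0.70 = 200 enrolments, before canteen exclusions, absence or unusable photographs.
- The article's Background reports 1462 pilot lunchboxes in 12 schools, about 122 per school. That makes a mean near 120 a reasonable lower scenario, though those were different schools.

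**4. Unequal school sizes under the planned model.** A hierarchical linear model weights each school by its information. The relative efficiency is approximately 1 − CV² × L × (1 − L), with L = m / (m + (1 − ICC)/ICC) = m / (m + 19). The CVs and the mean of 120 are assumptions; the document gives neither.

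| Mean analysed per school | CV | Relative efficiency | SE (kJ) | Power, t on 34 df | Detectable difference (kJ) |
|---|---|---|---|---|---|
| 140 | 0 | 1.000 | 71.5 | 77.6% | 206 |
| 140 | 0.3 | 0.990 | 71.8 | 77.2% | 207 |
| 140 | 0.6 | 0.962 | 72.9 | 76.0% | 210 |
| 120 | 0.3 | 0.989 | 72.6 | 76.3% | 209 |
| 120 | 0.6 | 0.958 | 73.8 | 75.0% | 213 |

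Exact weights over gamma-distributed school sizes give almost the same: 75.7% at mean 140 with CV 0.6, and 74.7% (about 214 kJ) at mean 120 with CV 0.6.

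**5. Loss of whole schools, 140 pupils each, t reference.** 17 per arm: 75.1%. 16 per arm: 72.3%.

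**6. What baseline adjustment could return.** If an assumed overall baseline correlation r scales the variance by 1 − r², then at 36 × 140 with t on 34 df, r = 0.25 gives 80.1% and r = 0.3 gives 81.3%.

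**The case against.** The strongest reply is that nothing has been miscalculated. The stated 80% follows from the stated inputs, and normal-approximation cluster formulas are common in planning. That stands: this is an optimistic calculation, not an arithmetic slip. But the t-based shortfall comes from the article's own inputs.

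A reader might infer that the plan cannot deliver 140 pupils per school. The document does not support that. The 120-enrolment criterion is a floor, larger schools can compensate, and nothing makes a mean enrolment of about 175–200 or somewhat more unlikely. Power is also fairly insensitive to pupils per school at this ICC: at 36 equal schools of only 84 analysed pupils it is still 74.4% on the t basis.

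A reader might also infer that unequal schools push power down to about 65–69%. Figures that low come from the design effect 1 + ((1 + CV²)m − 1) × ICC with CVs of 0.5–0.6. That formula describes an analysis that does not weight schools by their information, whereas the Analysis section specifies a hierarchical model. Under that model, size variation costs roughly 0.5 to 2 points.

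Nor does the abstract's wording amount to a plan for 30 schools, since recruitment continues until 36 consent.

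The planned model adjusts for prognostic variables and includes repeated measures on pupils, so baseline data may restore 80%. That is a fair point, but the sample size section claims no such gain and gives no correlation.

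Finally, a condensed article may leave attrition and size-variation allowances to a fuller document, so their absence alone is not the point. The point is that the article states a specific power that its own inputs, correctly referenced, do not reach, and that it leaves the key input of 140 undefined.

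**Conclusion.** The concern holds in a limited form. The 80% is the most favourable case: it needs a normal approximation, all 36 schools, and 140 analysed pupils in each. On the article's own inputs a t reference gives 77.6% (about 206 kJ). With realistic variation in school size under the hierarchical model, unadjusted power is about 75–77% (about 207–214 kJ), assuming a mean of 120–140 analysed pupils and a CV of 0.3–0.6. Losing one or two schools per arm costs more, giving 75.1% or 72.3% even with 140 pupils in each remaining school.

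This is a shortfall of roughly 2 to 5 points with all schools retained. It does not show the trial to be unsound, and a modest baseline correlation would offset the t correction. It is still worth correcting, because the article relies on the figure when it calls the trial fully powered.

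**What to change.** Restate the sample size section as follows.

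- Define 140 as analysed pupils per school.
- Use a t-based calculation on the between-school degrees of freedom.
- Use the expected mean and CV of analysed pupils per school, after consent, usable photographs and canteen exclusions, with mixed-model weighting.
- Quote the resulting unadjusted power (about 75–78%) or detectable difference (about 206–214 kJ), and the effect of losing a school per arm.
- Alternatively, state the baseline correlation relied on to reach 80%. At 36 × 140, an overall correlation of about 0.25–0.3 would give 80–81%; the value needs support from the pilot.

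In the abstract's Methods, replace the upper-limit wording with 36, to match Design, Sample and participants, Recruitment and the sample size section.

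The cost is wording and a slightly less favourable stated figure. No extra schools are needed.
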